#### Secondary: Self-report

Additional relevant outcomes included a broad range of validated self-reported outcomes related to neurobehavioral function, mood, and quality of life (e.g., NIH PROMIS Global Health, Pain Intensity/Interference, and Emotional Distress Anxiety [59,60]; Neurobehavioral Symptom Inventory, NSI [61]; Post-traumatic Stress Disorder Checklist for DSM-5, PCL-5 [62]; Patient Health Questionniare-9, PHQ-9 [63]; World Health Organization Disability Schedule 2.0, WHO-DAS 2.0 [64]; and Sleep Hygiene Index, SHI [58]). On average, this questionnaire battery required 30–45 minutes to complete. Questionnaires were completed using REDCap, with all entries automatically recorded. If participants were unable to complete questionnaires electronically, these were printed, mailed and all entries manually recorded into REDCap with a secondary rater confirming data entry accuracy.

#### Secondary: Cognition

Neurocognitive outcomes were assessed with both subjective and objective measures, and evaluated through neuropsychological testing (pre-, post-, and follow-up). This assessment was ~30 minutes in length and completed during a video call evaluating memory, attention, executive function, language and processing speed (e.g., Delis-Kaplan Executive Function System (D-KEFS) Verbal Fluency [65]; Controlled Oral Word Association Test, COWAT-FAS [66]; Wechsler Adult Intelligence Scale, Fourth Edition, WAIS-IV, Digit Span Arithmetic subtest [67]; Hopkins Verbal Learning Test–Revised, HVLT-R [68]. The HVLT-R implemented Form 1 pre-intervention and on follow-up, with Form 4 for post-intervention. This evaluation was also recorded for the accurate transcription of participant responses.

#### Secondary: Biomarkers

This protocol evaluated biofluid-based biomarkers associated with changes in sleep quality. Prior to the COVID-19 pandemic, this was accomplished through blood draws with appropriate processing to store serum/plasma aliquots (the first n = 30 participants). However, during the months of March 2020 and onward, the study pivoted to a fully remote protocol and as such, implemented sweat patches (PharmChek, Fort Worth, TX, USA) as a means to assay a comparable scope of blood-based biomarkers that were implicated in our prior pilot study on light therapy and sleep in TBI [25]. Assays included markers of neuroinflammation and degeneration (e.g., Neurofilament Light Chain, NfL; Glial Fibrillary Acidic Protein, GFAP; Ubiquitin Carboxyl-Terminal Hydrolase L1, UCH-L1; and total Tau, t-Tau), as well as markers of systemic inflammation (e.g., Interleukin-6, IL-6; Interleukin-10, IL-10; and Tumor Necrosis Factor-alpha, TNF-α). Participants were instructed to affix the sweat patch on their lower abdomen, after cleaning the area with an alcohol swab, and to keep the sweat patch on for 24 hours. Once the 24-hour period was complete, the sweat patch was removed, placed in a labeled plastic bag, and stored in the participant’s freezer. All sweat patches (pre-, post-, and follow-up) remained in the participant’s freezer until the end of the follow-up period, when they were provided with a pre-paid FedEx cold-shipping box (FedEx Nanocool) maintaining an internal temperature of ~4C for up to 96 hours to send the samples back to the study site. Upon receipt, the internal temperature was confirmed and sweat patches were stored at -20C until ready for batch assays.

#### Secondary: Dim Light Melatonin Onset (DLMO)

The protocol instructed participants to complete a salivary Dim Light Melatonin Onset (DLMO) protocol for the evaluation of changes in circadian alignment [69,70]. Detailed instructional guides reviewing the protocol were provided, a pair of blue wavelength blocking glasses, a toothbrush, and seven cotton-filled salivettes were provided. Samples were collected hourly for 5 hours prior to habitual bedtime, at bedtime, and one-hour post-habitual bedtime (i.e., participants stayed awake for 1 hour later than their habitual bedtime to provide 7 samples across 7 hours). Participants were advised to shutter blinds and turn off/dim lights while also wearing blue wavelength blocking glasses throughout the duration of this assessment, with objective light exposure also captured via the actiwatch’s luxometer. Also, participants were asked to refrain from alcohol for 72 hours before collection, and before each sample, remain seated and lightly brush/rinse their mouth with water (toothpaste/mouthwash is not allowed). Each sample was labeled and stored in the participants freezer until conclusion of follow-up whereby all three sets of samples were returned via the aforementioned temperature-controlled shipping container, following triple containment guidelines set by the Department of Transportation for biological samples. Upon receipt, internal temperature was confirmed and DLMO samples were processed according to standard procedures, aliquoted, and stored at -80C.

#### Secondary: Genetic analyses

Lastly, the protocol included the collection of an Oragene DNA sample (DNAgenotek, Ottawa, Ontario, CA) that consisted of ~2 ml of saliva. Participants avoided eating and drinking for 30 minutes before collection. Samples were considered stable at room temperature and therefore returned when convenient, generally occurring when participants returned their baseline period actiwatch.

### Shipping

The United States Postal Service (USPS) served as the primary courier for LION study packages to and from the participant’s home (Fig 2). The protocol specified that USPS flat rate boxes would be sent before baseline and intervention periods that contain all necessary instructions and equipment. Pre-paid return labels were already affixed underneath the primary delivery label. Unforeseen weather or other events preventing USPS from delivering these shipments on time was monitored and research coordinators rescheduled study visits if needed. Delivery of each shipment occurred before the baseline visit and before the onset of intervention (which includes randomized study arm device), with equipment returned using the same physical box it was received in. If needed, replacement return boxes were sent. Finally, at the end of the follow-up period, study coordinators sent the aforementioned FedEx cold-shipping box to return biospecimens. Receipt of returned equipment occurred following baseline and intervention. Study coordinators sanitized actiwatches with a 10% bleach solution followed by a 70% isopropyl alcohol solution, and downloaded the data to our Philips Actiware database after which it was charged and reconfigured for a new participant. Intervention devices were similarly sanitized and repackaged into protective storage containers.

### Data safety, monitoring and auditing

#### Study sponsor monitoring

The study sponsor, MTBI^2^, was responsible for maintaining quality assurance and accuracy of data collection, approved modifications, reviewed secondarily to our local IRB, and monitored our study site and study personnel to ensure ethical research conduct. The sponsor conducted in-person or remote monitoring visits twice per year, in which a study monitor from MTBI^2^ reviewed deidentified data, required reporting documents and the timeline of the study. Deidentified data and regulatory documents were stored on MTBI^2^’s data collection website, Collection Access Sharing Analytics (CASA), and hosted at the NIH for ease of access to monitors. A physical copy of regulatory documents was maintained at the site location. Study coordinators used the resources on MTBI^2^’s CASA to generate Globally Unique Identifiers (GUIDs) for the participants (using participant’s full name, date of birth, city they were born in); a master key list was maintained by study personnel and coded data are kept separate from personal health information.

#### OHSU Oregon Clinical and Translational Research Institute (OCTRI)

OCTRI hosted and managed data security and backup of the HIPAA-compliant REDCap database where our participant response data were stored. They have checks and balances coded into the database to allow for proper data protection, historical information and qualitative notes to be maintained. Access was protected via OHSU login information and user credentials once the database was shared from previously approved study personnel. This database is HIPAA-secure and all those interacting with the database are trained and knowledgeable of HIPAA and VA privacy policy.

### Statistical analyses

The statistical analysis plan was designed to be carried out using GraphPad Prism v9 or R, with alpha defined *a priori* at 0.05, using a thorough descriptive analysis of participant baseline characteristics prior to evaluation of outcomes. Categorical variables will be described using frequencies and percentages. Histograms and boxplots will be used to assess the distribution of continuous variables. Continuous variables that follow an approximately normal distribution will be summarized using means and standard deviations; skewed continuous variables will be reported as medians and interquartile ranges. Potential covariates will also be summarized with descriptive statistics and graphs. As part of our descriptive analyses, we will compare participants who complete versus drop out of the study by baseline characteristics and study arm to ascertain potential biases that may impact this and future studies. Effect size estimates will be reported as Cohen’s d (small = 0.2; medium = 0.5; large = 0.8) or standardized regression coefficients (β) (small = 0.14; medium = 0.39; large = 0.59). We will also report the number needed to treat (NNT) approximated using methods described by Kraemer and Kupfer [71]. The Benjamini-Hochberg procedure will be used to control the false discovery rate for primary outcomes. Statistical outliers will be identified using regression diagnostics to estimate Cook’s Distance, and then a cutoff of 4/n (n = number of participants) will be used to identify outliers. Outliers will be examined for data entry errors, but otherwise retained in analyses. If data violate parametric assumptions via Shapiro-Wilk test, test statistics will be derived using robust standard errors. We will use the intent-to-treat principle and include all participants randomized to treatment irrespective of treatment compliance.

To analyze treatment effect over time (pre-, post-, and follow-up), we will implement mixed effects models (either linear or gamma, pending data normality) for each outcome measure under consideration. This flexible approach allows us to examine the change pattern and accounts for within-subject correlations over multiple time points. This approach also maximizes our observed data by way of accommodating missing data at random. The main effects in each model will be the treatment and time effects, including a treatment-by-time interaction effect. The models may be adjusted for possible confounders, such as age, sex, fidelity adherence (lux/min), geographic location/seasonality, sleep hygiene, and depression. With a significant omnibus test suggesting the global null hypothesis is rejected, a Bonferroni or Tukey HSD post-hoc analysis will be performed.

Within the MBLT group we will use linear regression to analyze the relationship (goodness of fit; r^2^) between average morning lux exposure (quantified as lux/min by the Actiwatch) and the degree of change in dependent variables (e.g., sleep efficiency, self-reported sleep quality, neurocognitive outcomes, and other self-reported functional outcomes) between pre- and post-treatment. Within select patient outcome questionnaires, we will perform Pearson correlational analyses to determine how each patient outcome questionnaire varies together (Pearson correlation coefficient; r). Actigraphy variables will be compared to appropriate self-report and objective outcomes in the form of discrete time-period averages (i.e., 3–5 consecutive representative nights within the last ~7 days of both the baseline and intervention periods). Secondarily, if permissible, we will implement analyses based on a 3-day moving average, leveraging the unique frequency of data acquisition inherent to 24/7 actigraphy.

We will examine patterns of missingness in outcomes over time. Every effort will be made to minimize the risk of systematic missing data. Sensitivity analyses will be performed to assess the influence of missingness and attribute this to either "Random" or "System" causes (appreciating that data are rarely missing completely at random). These analyses will inform the robustness of our findings and potentially obtain better estimates of the magnitude of effects to inform future trials. We will follow the recommendations by Jakobsen et al.[72] to handle missing data for our assessment: (1) <5% without evidence of differential patterns of missingness we will consider this negligible and impute the “best” and “worst” case scenarios for missing data to estimate plausible ranges of MBLT and placebo effects. (2) 5–25% we cue implementation of Markov Chain Monte Carlo (MCMC) multiple imputation to impute missing values and analyze 5 combined imputed datasets. (3) >25% (unlikely) we will not attempt to impute missing values. In the case of (3), the results of the complete case analyses will be reported along with reasons for missingness. In all cases, we will discuss and report the extent of missingness with a clear discussion of study limitations.

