**Fig 1 pone.0305305.g001:**
[figure not shown]
SPIRT outcomes across time. The Standard Protocol Items: Recommendations for Interventional Trials (SPIRIT) timeline for LION.

The total target sample size of n = 120 participants is based on a priori power analyses considering mean insomnia severity index score as the primary outcome (see below). Using a two-sided students t-test design comparing MBLT to sham (pre- to post-intervention), the minimal detectable clinically relevant between-group difference was set at 7% with a standard deviation of 12% within MBLT and 7.3% within sham groups. This approach achieves β = 0.15 with α = 0.05 (i.e., 85% power; 15% probability of incorrectly accepting the null hypothesis) [49,50].

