**Fig 3 pone.0305305.g003:**
[figure not shown]
CONSORT diagram. The Consolidated Standards of Reporting Trails (CONSORT) diagram for participants in LION to date.

Justification for the unequal allocation ratio stems from the ethical recognition that the sham control confers no physiological benefit, whereas the active condition does [51]. However, using prior work as precedent, we anticipate greater variability in the MBLT group within key outcome metrics and thus, a 2:1 allocation ratio actually increases (albeit nominally) statistical power. Thus, this 2:1 allocation ratio is superior from an ethical perspective and better characterizes treatment dimensions in the MBLT group, ensuring the judicious use of federal funding.

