### Outcomes

#### Primary

LION’s primary outcome was designated as an improvement in sleep following MBLT compared to sham. This was accomplished via several means, though self-reported sleep disturbances via the Insomnia Severity Index (ISI) remained primary [53]. The ISI is a 7-item measure, each item a 5-point Likert scale (0–4) with a total score range of 0–28 where higher scores indicate worse sleep [54,55].

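### Robust standard errors are triggered by a normality test although the plan predicts unequal arm variances, and the gamma option cannot take an ISI of 0

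*Protocol article*

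**What the plan says.** All references are to the protocol article.

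- **Sample size** (Overview and ethics, below Fig 1): a two-sided Student t-test on the pre-to-post comparison, for which "the minimal detectable clinically relevant between-group difference was set at 7% with a standard deviation of 12% within MBLT and 7.3% within sham groups". The power statement is "This approach achieves β = 0.15 with α = 0.05 (i.e., 85% power; 15% probability of incorrectly accepting the null hypothesis".
- **Allocation** (Randomization, allocation, and masking, below Fig 3): the 2:1 ratio is justified mainly on ethical grounds, with a statistical remark: "we anticipate greater variability in the MBLT group within key outcome metrics and thus, a 2:1 allocation ratio actually increases (albeit nominally) statistical power".
- **Robust errors** (Statistical analyses, first paragraph): "If data violate parametric assumptions via Shapiro-Wilk test, test statistics will be derived using robust standard errors".
- **Efficacy model** (Statistical analyses, second paragraph): "we will implement mixed effects models (either linear or gamma, pending data normality) for each outcome measure under consideration". No residual covariance structure and no link function are stated.
- **Primary scale** (Outcomes, Primary): the ISI has a "total score range of 0–28 where higher scores indicate worse sleep". The section Eligibility criteria lists no minimum ISI for entry.

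**The concern.** The plan states twice that the arms will differ in variance: in the sample-size inputs and in the reason given for 2:1 allocation. Its rule for leaving default standard errors looks at something else. Two normal samples with SDs of 12 and 7.3 satisfy normality in each arm and still violate the equal-variance assumption of a Student t-test.

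With the larger variance in the larger arm, a pooled standard error is too large. Intervals are then too wide and some power is lost. The remark that 2:1 raises power also depends on the kind of standard error used, and the plan does not make the kind that it needs the default.

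A second weakness sits in the same rules. Non-normality may lead to a gamma model for any outcome, including the primary one. A gamma distribution has strictly positive support, whereas an ISI of 0 is a valid score and a possible one after successful treatment.

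**Working it through.** **Inputs from the article.** Difference 7%; SD 12% (MBLT) and 7.3% (sham); n = 80 and 40; two-sided alpha 0.05; stated power 85%. The variances are 144 and 53.29, a ratio of 2.70.

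**1. The plan's own power figure.**
- With both stated SDs, SE = √(144/80 + 53.29/40) = √(1.800 + 1.332) = 1.770. Then 7/1.770 = 3.955, and power is 97.5% (Welch t). This is not 85%.
- With a common SD of 12 in both arms, SE = 12 × √(1/80 + 1/40) = 2.324. Then 7/2.324 − 1.96 = 1.052, and power is 85.4%.
- So 85% at N = 120 is reproduced by a common SD of 12, that is, without using the 7.3%. On that basis 1:1 would give SE = 12 × √(2/60) = 2.191 and power 89.2%, so the sizing calculation that matches does not favour 2:1 either.

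**2. Equal-variance error under the stated SDs, 80/40.**
- Pooled variance = (79 × 144 + 39 × 53.29)/118 = 114.02, so the pooled SD is 10.68.
- Pooled SE = 10.68 × √(1/80 + 1/40) = 2.068.
- Ratio to the true SE = 2.068/1.770 = 1.168, about 17% too wide.

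**3. Operating characteristics** (40,000 simulated two-arm trials per setting with normal data, and noncentral t for Welch power):

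| | Equal-variance test | Unequal-variance test |
|---|---|---|
| Type I error, 80/40 | 2.3% | 5.0% |
| Power for 7%, 80/40 | about 95% | 97.5% |
| Power for 7%, 60/60 | 97.0% | 96.9% |

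With unequal-variance errors 2:1 gains about 0.6 points over 1:1. With pooled errors it loses about 2 points. The gain is small because the ratio that minimises the SE is 12/7.3 = 1.64, which lies between 1:1 and 2:1: the true SE is 1.770 at 80/40 and 1.813 at 60/60.

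**4. Three-visit mixed model.** The article gives no covariance structure, so two were assumed. Each had a random intercept (SD 12), a change SD of 12 on MBLT and 7.3 on sham, and 200 simulated trials; a common residual variance was fitted.
- Residual SDs differ by arm (12/√2 and 7.3/√2): mean model SE 2.055 against 1.770, ratio 1.16.
- Common residual SD, with the extra MBLT spread as a persistent individual response, SD √(144 − 53.29) = 9.52: mean model SE 1.878 against 1.770, ratio 1.06.

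**5. Gamma at 0.** The log-density contains (k − 1) × log(y), where k is the shape. As y approaches 0 this tends to minus infinity for k > 1 and to plus infinity for k < 1. One ISI of 0 therefore leaves the likelihood unusable. Nothing in the scale or the listed entry criteria rules out a 0.

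**The case against.** The Student t-test appears only in the sample-size paragraph; efficacy is to be tested with a mixed model whose residual structure a condensed article may leave to the full plan. That stands. A reader might take the 17% as the error of the planned analysis, but the article does not show that the model will assume a common variance. The figure belongs to the two-arm comparison and is conditional on equal-variance errors.

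Other stronger readings are tempting and also fail:

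- **Inflated false positives or an underpowered trial.** Under the stated SDs the error runs the other way, and power for the 7% difference stays above 85%. Type I error would rise only if sham were the more variable arm, which is the opposite of what the plan predicts.
- **Robust errors would rarely be used.** Shapiro-Wilk rejects in about 11% to 12% of simulated trials with one exactly normal value per person. The ISI is an integer score measured at three visits. Under assumed rounding, repeated visits or modest skew the rate ran from 24% to 61%. The documents fix no rate.
- **The 2:1 statement is wrong.** It is correct with unequal-variance errors, is called nominal, and is secondary to the ethical argument.
- **Two contradictory remedies for non-normality.** The rules can coexist: choose the model family, then use robust errors if misfit remains.
- **Gamma turns the effect into a ratio.** That needs a log link, and no link is stated.

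What survives is that a normality test is the only stated trigger, that nothing ties it to the predicted variances, and that gamma is open to a scale that includes 0.

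**Conclusion.** The point holds as a mismatch between the plan's variance assumption and its stated analysis rule. If equal-variance errors are used, the pre-to-post SE is about 17% too wide in the two-arm comparison, or roughly 6% to 16% too wide in the three-visit model under the two assumed covariance structures. The cost is precision and about 2.5 points of power (about 95% against 97.5%), together with the statistical basis for the 2:1 remark. Validity is not threatened in the direction that matters most, since type I error is about 2%.

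These sizes rest on the stated SDs, the full 80/40 sample and normal data. The gamma problem is separate and conditional: it arises only if that branch is chosen for the ISI, or for another scale that includes 0, and at least one 0 is observed. The change is worth making because it is nearly free, but this is not a fatal flaw.

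**What to change.** For score outcomes, prespecify a linear mixed model with arm-specific residual variances, or small-sample-corrected robust standard errors, and apply it regardless of the Shapiro-Wilk result. Remove the gamma option for any scale that can be 0, such as the ISI. Report the treatment effect as a difference in points. The 2:1 power remark is then consistent with the analysis.

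The cost is one model specification. GraphPad Prism may not fit it; R, which the plan already names, does. If the arm variances prove equal, the loss of precision is negligible. The Results section says that formal analyses of primary and secondary outcomes had not been explored, so at that stage the change could still be prespecified.

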To our knowledge, the field of sleep medicine is without a fully powered, sham-controlled, masked, randomized controlled trial establishing feasibility, acceptability and efficacy of MBLT to improve sleep quality in Veterans with mTBI. Furthermore, to our knowledge, a fully remote randomized controlled trial device intervention protocol has not yet been successfully implemented in Veterans with mTBI–a challenging population not only due to significant participant disability/burden, but also due to the logistical and regulatory challenges of device management and electronic data capture behind the Veterans Affairs (VA) firewall. We sought to fill both gaps by implementing LION (Light vs Ion therapy), whose protocol is described herein. This trial proposed to acquire complete data in n = 120 Veterans allocated 2:1, active-intervention (MBLT, n = 80) versus sham-intervention (deactivated ion therapy, n = 40). MBLT delivered white light (10,000 lux at the eye), whereas the negative ion generator was fully deactivated, but modified to appear “on”, i.e., via installation of a small fan to generate a quiet, whirring sound, as well as a small LED status light. This sham-intervention was modeled from prior work by Lam et al., [28] in which bright light or sham-intervention therapy was compared to fluoxetine for the treatment of depression. Participants in both groups engaged with devices to the same extent (i.e., over 60 minutes within 2 hours after waking) throughout the 28-day intervention period, with the same degree of expectancy and study team interaction. The brand of the light box was chosen due to being commercially available, in use for decades (including within the VA), and previously validated for illuminance metrics and spectral power density [25]. Dose, timing, and duration were all established from prior work investigating the effect of MBLT for the treatment of insomnia, circadian entrainment, and seasonal affective disorder [46–48].

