### Eligibility criteria

Eligibility criteria for enrollment included, over 18 years of age, able to provide informed consent and comply with the study protocol, no history of macular degeneration (contraindicated due to light therapy potentially exacerbating underlying pathology), no history of bipolar disorder (contraindicated due to light therapy potentially inciting a manic/depressive episode [31]), no shift work on third shift (e.g., 2300–0700 or equivalent) or any amount of days overnight, no current engagement in light therapy, and stable status on other pharmacological and/or behavioral sleep interventions.

This study originated in an in-person format with an exclusive focus on Veterans with mTBI, however protocol #4268 was amended to be conducted remotely, and expand recruitment to non-Veterans and to non-TBI participants, for the express purpose of increasing the diversity of this sample in terms of the number of women and individuals from racial/ethnic minority groups and increasing overall generalizability. See Table 1 for demographic parameters describing this current interim analysis.

History of mTBI was confirmed through a structured clinical interview using the Head Trauma Events Characteristics (HTEC; Table 2). The HTEC consists of a standard screening question followed by branching logic questions addressing injury type, location, intracranial injury/skull fracture, duration of loss of consciousness (LOC), and anterograde or retrograde post-traumatic amnesia (PTA), conferring a diagnosis of no, mild, moderate or severe TBI. Participants with an affirmative TBI outcome on the HTEC were excluded if their injury was moderate to severe and thus, the study only included participants with a history of mTBI. However, participants screening negative for TBI on the HTEC who met all other eligibility criteria, were also offered enrollment to promote generalizability throughout the wider VA.

**Table 2 pone.0305305.t002:** Current HTEC derived mTBI metrics.

	MBLT (*n* = 69)	Sham (*n* = 35)
	mTBI (n = 47)	mTBI (n = 24)
**Age at injury,** *years*	28.2 ± 17.4	29.6 ± 16.0
**mTBI recency,** *years*	26.2 ± 20.8	20.3 ± 15.0
**mTBI recency range**, *years*	2–67	1–52

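### Baseline ISI enters the planned model only as the first repeated response, so the linear pre-to-post contrast is a change-score difference and less precise than a baseline-adjusted one

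*Protocol article*

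**What the plan says.** All references are to the protocol article.

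- **Outcome.** Outcomes, Primary, makes the ISI the leading measure, with a "total score range of 0–28 where higher scores indicate worse sleep". The next subsection makes pre- versus post-intervention the main comparison over time.
- **Model.** Statistical analyses fits mixed models (linear or gamma, depending on the distribution) to the three time points. On the fixed effects it says: "The main effects in each model will be the treatment and time effects, including a treatment-by-time interaction effect".
- **Covariates.** The same paragraph allows, but does not require, adjustment. It gives examples that include age, sex, adherence, location or season, sleep hygiene and depression. Baseline ISI is not among them.
- **Entry.** Eligibility criteria lists age, consent, eye disease, bipolar disorder and shift work, and ends with "no current engagement in light therapy, and stable status on other pharmacological and/or behavioral sleep interventions". No minimum ISI or sleep complaint is listed.
- **Sample size.** Overview and ethics gives a t-test with a 7% difference and "a standard deviation of 12% within MBLT and 7.3% within sham groups", and concludes: "This approach achieves β = 0.15 with α = 0.05".

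**The concern.** Randomisation makes the two arms equal at baseline in expectation. A model with a free treatment main effect ignores this: it estimates a baseline arm difference and subtracts all of it from the post-intervention difference. Unless the slope of post on baseline ISI is 1, that subtracts too much or too little and adds noise to the primary contrast. The trial already collects the variable that would remove this noise, and the named covariates leave it out. What is at stake is precision on the primary outcome in a 2:1 trial of 120, not validity.

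**Working it through.** **Inputs.** From the article: 80 versus 40 participants, difference 7%, SDs 12% and 7.3%, two-sided alpha 0.05, stated power 85%. Assumed: pre-post correlation of ISI, rho = 0.3, 0.5 or 0.7, because the article gives none.

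**1. The plan's own figure.** With both printed SDs, SE = sqrt(12²/80 + 7.3²/40) = sqrt(1.800 + 1.332) = 1.77. Then 7/1.77 = 3.955, and power is Φ(3.955 − 1.960) = 97.7% (97.5% by Welch t). With 12% in both arms, SE = 12 × sqrt(1/80 + 1/40) = 2.32, and power is 85.4%. So the stated 85% appears only if the 7.3% is set aside. That is a separate matter, and the gains below are shown from both starting points.

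**2. What the interaction estimates.** With complete data at two times and a free baseline arm difference, the treatment-by-time estimate is (post − pre in MBLT) − (post − pre in sham). In one simulated data set, the fitted mixed-model interaction and the change-score difference were both −3.236. The SE was 1.03, against 0.92 with baseline as covariate.

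**3. Variance ratio.** With equal pre and post variance σ² and the same covariance in both arms:
- change score: variance proportional to 2σ²(1 − rho)
- baseline-adjusted: variance proportional to σ²(1 − rho²)
- ratio: (1 − rho²) / [2(1 − rho)] = (1 + rho)/2
- SE reduction: 1 − sqrt((1 + rho)/2)

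**4. Results.** The simulation used 4000 runs per rho with 80 versus 40. The participant count is 120 × ratio. Power from 85% is Φ((1.960 + 1.036)/sqrt(ratio) − 1.960). Power from 97.5% treats the printed SDs as SDs of change.

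| rho (assumed) | Ratio, formula | Ratio, simulated | SE lower by | Participants for same precision as 120 | Power from 85% | Power from 97.5% |
|---|---|---|---|---|---|---|
| 0.3 | 0.65 | 0.66 | 19% | 78 | 96% | 99.8% |
| 0.5 | 0.75 | 0.76 | 13% | 90 | 93% | 99.5% |
| 0.7 | 0.85 | 0.86 | 8% | 102 | 90% | 98.9% |

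**5. If pre and post SDs differ.** Write s0 and s1 for these SDs. The change-score variance minus the adjusted variance is (s0² + s1² − 2·rho·s0·s1) − s1²(1 − rho²) = (s0 − rho·s1)². With a common covariance in both arms this is never negative. It is zero only when the slope of post on baseline, rho·s1/s0, equals 1.

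**6. Data available.** Table 3 gives pre-intervention ISI in 47 + 22 + 24 + 11 = 104 of 104, and post-intervention ISI in 43 + 17 + 21 + 10 = 91 of 104. That leaves 13 without a post-intervention score.

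**The case against.** **Much of this belongs in an analysis plan.** Covariates are offered by way of example, so baseline ISI is not excluded, and an article may leave the final list elsewhere. This stands in part: the point is not that adjustment is forbidden. But the article does state the fixed effects, and as stated they give a change contrast.

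**Baseline is not ignored, and the estimate is valid.** Both are true. Baseline ISI is in the model as a response, and the change contrast already subtracts a chance baseline difference. What remains is regression to the mean: with equal variances, an observed baseline difference D shifts the contrast by −(1 − rho)·D. The choice is between two valid methods that differ in efficiency.

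**The size is uncertain.** It rests on an assumed rho and equal variances, and at rho 0.7 the gain in SE is only 8%. The formula does not carry over to the gamma option. This stands; the gain is a range.

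**A reader might infer more from the entry criteria:** that a floor effect is present, that the 7% target is diluted by people who cannot improve, or that a null result could not be told apart from a floor effect. The article does not support these readings.
- No baseline ISI distribution is reported, so no share of participants near the floor can be stated.
- Strictly, only an ISI of 0 leaves no room to improve.
- Nothing says that the 7% was meant only for people able to respond; it is the planned difference between the arms.
- Baseline histograms and boxplots are planned before outcomes are evaluated, so clustering near zero would be visible.
- The criteria are given in condensed form, so a threshold missing from the list does not prove that none exists.

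A covariate alone would not undo dilution in any case.

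**Conclusion.** The point holds as one of efficiency. In its linear form with a free baseline arm difference, the stated model gives an unbiased but less precise pre-to-post contrast than a baseline-adjusted or baseline-constrained analysis. Over rho 0.3 to 0.7 the variance could be cut by 35% to 15%, and the SE by 19% to 8%. This assumes two complete time points, equal pre and post variances and a common covariance in both arms. Effects on power are modest if the printed SDs are SDs of change (97.5% to at least 98.9%) and larger if the stated 85% is the true starting point (to 90–96%). Bias, a floor effect and dilution of the 7% target are not shown. What the entry list does support is a reporting point: the pooled effect applies to a sample for which no insomnia threshold is listed.

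**What to change.** For the primary ISI comparison, prespecify one of two analyses:

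1. a mixed model of pre-, post- and follow-up ISI with the arm means constrained equal at baseline; or
2. a model with post and follow-up ISI as outcomes and baseline ISI as covariate.

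The constrained model has the advantage that it keeps participants without a post-intervention score, 13 of 104 in Table 3.

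A single treatment-by-baseline-ISI term may be added, labelled exploratory; a 2:1 trial of 120 has little power for it, and effects in several severity bands are not needed. In the report, state that the pooled effect applies to a sample for which no insomnia threshold is listed.

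The cost is wording in the analysis plan. Baseline ISI is already collected and complete in all 104, and eligibility, recruitment and visits do not change. The Results section says that outcomes had not yet been analysed, so at the time of the article the choice could be made without knowledge of the results.
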